#### Secondary outcome

The time to reach enteral nutrition (parenteral nutrition), length of hospital stay, meconium drainage time during the NICU stay will be summarized and compared using Kaplan-Meier estimators and logrank tests. Cox models will also be fitted for time-to-event data adjusting for baseline covariates. The number of times of self-defecating per day will be compared using the Poisson model adjusting for baseline covariates. The rates of comorbidity will be compared using Poisson models. The plasma total protein, albumin level, calcium, alkaline phosphatase levels before discharge from the NICU will be compared using *t* tests. Growth rates measure by weight, body length, and head circumference during the NICU and within 3 months of discharge will be analyzed using repeated measurement analysis of covariance models. All analysis will be conducted using SAS 9.4 (SAS Institute, Cary, NC, USA).

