Criteria for discharge from the NICU or transfer to direct rooming-in (DRI):Corrected gestational age ≥34 weeks, and weight ≥1500 gNo need for oxygen inhalation, stable vital signs, no apnea phenomenonAble to suck formula on their own, and coordinated sucking-swallowing-breathing actionHaving achieved full enteral feeding, daily milk volume ≥150 ml/kg, no need for any intravenous medicationAble to maintain normal body temperature at room temperature of 22–24 °CEach system is free from life-threatening pathological conditionsBirth weight has been restored, and weight begins to grow steadily

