### Study design and outcomes

#### Outcomes

The first endpoint variable is the rate of food intolerance in preterm children. The second endpoint variables include (1) time to achieve full enteral nutrition; (2) time of parenteral nutrition; (3) time of NICU stay; (4) meconium drainage time; (5) daily spontaneous fecal discharge conditions; (6) growth and development conditions during the NICU stay and within 3 months after discharge, including daily weight growth rate, weekly body length growth rate and weekly head circumference growth rate; (7) different plasma parameter indicators before discharge from the NICU (total protein (TP), albumin, calcium (Ca), phosphorus (P), and alkaline phosphatase (ALP)). Other endpoint variables include the incidences of neonatal necrotizing enterocolitis, cholestasis, parenteral nutrition-associated cholestasis and congenital hypothyroidism (CH).

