#### Introduction to the formulae

The two kinds of formula for feeding during the NICU stay and the formula for feeding after discharge from the NICU are all Dumex, a brand of French Danone-Nutricia for early life nutrition. In this study, the gestational age of all preterm children when discharged from the NICU is all ≥34 weeks, and thus formula suitable for 0 to 6-month-old infants is uniformly chosen for them after discharge. The ingredients of such formulae are shown in Table 1.

**Table 1 Tab1:** Table of ingredients of the three formulae

Ingredients	Preterm children’s formula (/100 ml)	Extensively hydrolyzed formula (/100 ml)	Formula for 0 to 6-month-old infants (/100 ml)
Energy (kcal/KJ)	80/336	66/278	67/282
Osmolality (mOsmol/L)	360	250	-
Fat (g)	3.8	3.5	3.5
α-linolenic acid (mg)	44	58	42
Linoleic acid (g)	0.6	0.41	0.42
Oleic acid (g)	1.3	1.2	-
Medium-chain triglyceride content (%)	30 %	40 %	-
Protein (g)	2.6 (60 % whey protein and 40 % casein)	1.6 (100 % whey protein)	1.4
Carbohydrates	8.4	6.9	7.1
Lactose (g)	5.6	2.8	-
Prebiotics (galactooligosaccharides, polyfructose) (g)	0.8	0.8	0.8
Arachidonic acid (mg)	19	6.6	12
Docosahexaenoic acid (mg)	15	6.6	12
Taurine (mg)	5.5	5.3	5.4
L-carnitine (mg)	1.8	1	1.5
Nucleotides (mg)	3.4	3.2	3.0
Vitamin A (μg)	359	52	65
Vitamin D (μg)	3	1.3	0.95
Vitamin E (mg)	3.5	1	1.2
Vitamin K1 (μg)	6	4.7	5.4
Vitamin B1 (μg)	139	50	58
Vitamin B2 (μg)	199	99	103
Vitamin B6 (μg)	119	40	48
Vitamin B12 (μg)	0.24	0.18	0.31
Nicotinamide acid (μg)	2352	432	517
Folic acid (μg)	35	9	11
Pantothenic acid (μg)	876	327	354
Vitamin C (mg)	17	9	9.2
Biotin (μg)	3.5	2.2	2.3
Choline (mg)	17	10	16
Inositol (mg)	24	3.2	3.8
Sodium (mg)	70	20	20
Potassium (mg)	80	75	69
Copper (μg)	80	40	48
Magnesium (mg)	8	5.1	5.7
Iron (mg)	1.6	0.53	0.71
Zinc (mg)	1.1	0.5	0.5
Manganese (μg)	10	7.4	7.5
Calcium (mg)	100	47	52
Phosphorus (mg)	56	26	31
Iodine (μg)	25	12	11
Chlorine (mg)	85	41	48
Selenium (μg)	4.5	1.5	2.2

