### Collection of clinical data during the NICU stay

Collection of general data of the objects of study:Sex, gestational age, birth weight, birth head circumference, birth body length, mode of delivery, 5-minute Apgar score, etc., of preterm childrenMother’s pregnancy complications and comorbidities: premature rupture of membrane >24 hours, placental abruption, chorioamnionitis, pregnancy-induced hypertension syndrome, preeclampsia, gestational diabetes, hyperthyroidism, hypothyroidism, systemic lupus erythematosus, kidney disease, cholestasis, acute liver failure, syphilis infection, etc.Special treatment: nasal continuous positive airway pressure (nCPAP), intubation and mechanical ventilation (MV), use of pulmonary surfactant (PS), thoracentesis, bone marrow biopsy, thoracic drainage, peritoneal dialysis, etc.Collection of case data during the NICU stay:

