### Sample size justification

We calculate the sample size based on the chi-square test comparison of the food intolerance rate during NICU between groups. Our previous pilot study shows that the rate of food intolerance during NICU for control patients is about 85 %. We expect that the intervention group will have a reduced intolerance rate to be 75 %. With these assumptions, we will need 148 infants in each group to finish the NICU part of the study to reach 80 % power and 5 % Type I error rate. Assuming that the dropout rate to be 20 %, we will need to enroll 185 infants in each group.

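### NICU stay has a minimum length set by gestational age at birth, so its log-rank test and Cox model should be stratified by completed week of gestation

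*Protocol article*

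**What the plan says.** The Outcomes section lists as a secondary endpoint "3) time of NICU stay", and shortening that stay is part of the secondary objective. The analysis is fixed in the Secondary outcome section: "length of hospital stay, meconium drainage time during the NICU stay will be summarized and compared using Kaplan-Meier estimators and logrank tests". It continues: "Cox models will also be fitted for time-to-event data adjusting for baseline covariates". It does not name the covariates and mentions neither stratification nor another time scale.

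Three other places determine what a stay can look like:

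- The first NICU discharge criterion is "Corrected gestational age ≥34 weeks, and weight ≥1500" g.
- The section introducing the formulae says that "the gestational age of all preterm children when discharged from the NICU is all ≥34 weeks".
- The exclusion list removes infants discharged before they meet the criteria. Entry requires gestational age below 34 weeks, with no lower limit, and transfer to the unit straight after birth.

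**The concern.** An infant born at 28 weeks cannot be discharged for about six weeks; one born at 33 weeks can be after about one. That part of the stay is settled at birth. A log-rank test that pools all infants puts very different minimum stays into the same risk sets and treats the difference as noise, so a real reduction is harder to see.

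The same floor is awkward for a Cox model on days since admission. Between two infants of different gestational age, the hazard ratio is zero while only the older one can be discharged, and positive later. No constant ratio describes that. If gestational age is a covariate, the standard error of the treatment effect can come out too small.

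At stake is one secondary endpoint. A null log-rank result could be read as no benefit when the test was weak, and a significant adjusted result could be less secure than its p value suggests.

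**Working it through.** **1. The plan's own figures.** No effect size or power is given for NICU stay. The only calculation is for the primary endpoint: "we will need 148 infants in each group to finish the NICU part of the study to reach 80 % power and 5 % Type I error". It starts from a pilot in which "the rate of food intolerance during NICU for control patients is about 85" %, against 75 % expected. The standard two-sided formula gives [1.96·√(2·0.80·0.20) + 0.842·√(0.85·0.15 + 0.75·0.25)]² / 0.10² ≈ 250 per arm, not 148. That is a separate matter. Here 148 per arm (296 in all) is taken simply as the stated number of completers; 148/0.8 = 185 enrolled does reproduce.

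**2. The floor.** Minimum stay ≈ (34 − gestational age in weeks) × 7 days:

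- 28 weeks: 6 × 7 = 42 days
- 30 weeks: 4 × 7 = 28 days
- 33 weeks: 1 × 7 = 7 days

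**3. Assumptions.** The document gives no gestational-age distribution, spread of stay or treatment effect, so these are assumed and varied. Two stay models were simulated: additive (floor plus a gamma residual) and maximum rule (the later of the floor and a readiness time). Stays were rounded up to whole days, with no censoring, a 3-day effect and two-sided 5 % tests. Null runs used 2,000–4,000 trials, so the Monte Carlo standard error at 5 % is √(0.05·0.95/4000) = 0.003 to √(0.05·0.95/2000) = 0.005.

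**4. Log-rank power, 148 per arm.**

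| Gestational age (weeks) | Stay model | Pooled | Stratified by week |
|---|---|---|---|
| 26–34 | additive | 0.43–0.50 | 0.76–1.00 |
| 28–34 | additive | 0.64 | 0.96 |
| 26–34 | maximum | 0.19–0.26 | 0.43 |
| 30–34 | additive | 0.65 | 0.79 |
| 30–34 | maximum | 0.50 | 0.57 |

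A further simulation under its own assumed spreads gave 0.27–0.62 pooled against 0.80–0.87 stratified. With no true difference, the pooled test rejected in 0.043–0.061 of trials and the stratified test in 0.048–0.056, so both hold their level.

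**5. Type I error of the Cox model on days since admission, model-based variance, nominal 0.05.**

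| Covariate and setting | Rejection rate |
|---|---|
| Gestational age, additive, 26–34 or 28–34 | 0.13–0.18 |
| Gestational age, maximum, 26–34 | 0.09–0.10 |
| Gestational age, additive, 30–34 | 0.084 |
| Gestational age, maximum, 30–34 | 0.059 |
| Gestational age, floor hardly ever binds | 0.052 |
| Birth weight only, floor binding | 0.065–0.084 |
| Sex only | 0.050–0.058 |

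The mechanism shows in the null standard deviation of the test statistic. It was 1.37 in one wide additive setting instead of 1, so the effective cut-off is 1.96/1.37 = 1.43, which a standard normal exceeds in absolute value about 15 % of the time. Robust variance lowered the rate but left 0.09–0.12 where the floor was strong. Gestational week entered as a categorical covariate still gave about 0.13 in the wide additive settings. A Cox model stratified by week gave 0.04–0.06. The code matched a standard package and gave 0.047–0.050 on data with truly proportional hazards.

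**The case against.** An unadjusted log-rank comparison of randomised arms is valid and conventional, and the trial is not sized for NICU stay. This stands. A reader might infer that the planned test is biased or wrong; it keeps its 5 % level, and the issue is efficiency only.

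Covariates, functional form and variance estimator are commonly left to an analysis plan, which is not shown here. This also stands: leaving them unnamed is no fault. A reader might infer that the adjusted Cox model is anti-conservative as planned. The documents do not support that, because gestational age is not named as a covariate. It is a plausible one, since the baseline data listed for collection begin "Sex, gestational age, birth weight, birth head circumference", but a stratified model is not ruled out either. Nor do the results support false positives up to five times too often: at 148 per arm the highest rate was 0.18, or 0.18/0.05 = 3.6 times nominal, and several settings were close to nominal.

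The 34-week criterion is one of seven. Weight, milk volume, independent sucking and freedom from oxygen can all delay discharge, and some of these depend on feeding. A reader might infer that most of the variation in stay is fixed at birth. The document has no data on how often the 34-week criterion is the last one met, so that cannot be said.

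What the objection does not remove is the floor itself, which the document states, or the gain from conditioning on it.

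**Conclusion.** The point holds as a free improvement, not as an error in the plan. The floor follows directly from the discharge rule and the exclusions.

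The size of the power loss rests on assumed gestational-age spread, residual spread and a 3-day effect. It is modest with a narrow age range and the maximum rule (0.50 against 0.57), and more than half of the attainable power at the other end (about 0.3 against 0.8, ages 26–34).

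The Cox concern is conditional. With gestational age as a linear covariate on days since admission, type I error is about 6–18 % according to how often the floor binds. With covariates unrelated to gestational age it is about 5 %.

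**What to change.** State in the Secondary outcome section that, for NICU stay, both the log-rank test and the Cox model are stratified by completed week of gestation at birth. Gestational week should define strata, not enter as a covariate. Continue to report raw median days by arm, which is what clinicians will want to read.

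Restarting the clock at 34 weeks is not a full substitute. The log-rank test on that scale held its level (0.043–0.060), but a Cox model on that scale adjusted for gestational age reached 0.06–0.12 when the time past 34 weeks depended on gestational age.

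The cost is one sentence, settled before outcome data are examined. Gestational age and length of stay are already collected, and neither the discharge criteria nor any infant's care changes. Very sparse early weeks may need to be combined into one stratum, also fixed in advance.

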Incidence and outcome of feeding intolerance in preterm children, neonatal necrotizing enterocolitis, cholestasis, parenteral nutrition-associated cholestasis and congenital hypothyroidism3.Collection of enteral and parenteral nutrition and defecation conditions during the NICU stay:Milk opening time (h), total amount of daily milk (ml) and calories (kcal), total amount of daily parenteral nutrition (ml) and calories (kcal), total volume of daily fluids (ml) and total calories (kcal)The number of daily bowel movements, times of daily enema, trait and color of stool every time, meconium drainage time (h)Gastric residual volume (ml) and nature, times and nature of vomiting, and abdominal distensionTime to achieve full enteral nutrition (d), and total time of parenteral nutrition4.Collection of physical growth and development indicators during the NICU stay:Weight: weight will be measured at admission, once every day during hospital stay and before discharge with a baby electronic scale, and the data will be accurate to 10 g.Body length: body length will be measured at admission, once every week during hospital stay and before discharge, and the data will be accurate to 0.1 cm.Head circumference: head circumference will be measured at admission, once every week during hospital stay and before discharge, and the data will be accurate to 0.1 cm.5.Collection of laboratory indicators during the NICU stay:Daily monitoring of peripheral blood glucose and transcutaneous bilirubinWeekly detection of blood, liver and kidney function (total protein, albumin, total bilirubin, direct bilirubin, alkaline phosphatase, bile acids, alanine aminotransferase, aspartate aminotransferase, γ-glutamyl transferase, urea nitrogen, creatinine) and electrolytes (mainly calcium and phosphorus)Test of serum thyroid function 1–2 weeks after admission, including TSH, TT_3_, TT_4_, FT_3_ and FT_4_

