#### Primary outcome

The rates of food intolerance during NICU will be summarized and compared using the chi-square test. A *p* value <0.05 indicates a significant difference in rates between the two groups. We will also fit the logistic regression model with food intolerance status as the outcome variable, and group as the main predictor adjusting for covariates. In the case that the number of intolerance events is large enough, we will consider using a Poisson model to model the number of intolerances.

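### The only model named for daily stool counts is Poisson, with no allowance for repeated days on the same infant, so its standard error is generally wrong

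*Protocol article*

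**What the plan says.** The Outcomes section lists "daily spontaneous fecal discharge conditions" as the fifth secondary endpoint, and the secondary objective names spontaneous stooling as a hoped-for benefit. The section on collection of clinical data during the NICU stay shows how it is recorded, day by day for each infant: "The number of daily bowel movements, times of daily enema, trait and color of stool every time".

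The analysis is fixed in one sentence under Secondary outcome: "The number of times of self-defecating per day will be compared using the Poisson model adjusting for baseline covariates". No unit of analysis, offset, scale parameter, random effect or clustered variance is mentioned. In the same paragraph, growth, which is also measured repeatedly on each infant, "will be analyzed using repeated measurement analysis of covariance models".

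Poisson models appear in two other places. Under Primary outcome, if there are enough events, "we will consider using a Poisson model to model the number of intolerances". Under Secondary outcome, "The rates of comorbidity will be compared using Poisson models". The primary comparison itself does not use Poisson: "The rates of food intolerance during NICU will be summarized and compared using the chi-square test".

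**The concern.** A Poisson model sets the variance equal to the mean and treats the counts as independent. Daily stool counts on one infant are not independent. Some infants stool more often than others throughout their stay, and baseline covariates remove only the part of that variation which they explain.

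The article itself describes sources of difference between infants. Feed volumes vary by birth weight, feeding method varies by gestational age, some infants are fasted, and enemas are given. Fasting and enemas arise after baseline, so adjustment for baseline covariates does not capture them fully.

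At stake is the inference on one named secondary benefit. If the standard error is too small, a difference in stool frequency could be declared where there is none. If it is too large, a real difference could be missed.

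**Working it through.** **Plan's own figure.** There is none to reproduce. The documents give no mean stool count, dispersion, number of days or standard error for any Poisson analysis.

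**Assumed inputs.**
- Days observed m: 14–30. Discharge requires a corrected gestational age of at least 34 weeks, so an infant born at 32 weeks contributes at least (34 − 32) × 7 = 14 days, and one born at 30 weeks at least 28.
- Mean stools per day μ: 2–3.
- Between-infant coefficient of variation CV, after covariates: 0.2–0.5.

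**Infant-days or infant totals.** With only baseline covariates in the model, daily counts and infant totals with a log-days offset give the same group effect and the same Poisson standard error. If an infant's underlying rate varies with coefficient of variation CV, the total over m days has mean mμ and variance mμ + (mμ·CV)². Hence:
- variance inflation φ = 1 + m·μ·CV²
- true SE / Poisson SE = √φ
- actual two-sided type I error = 2·[1 − Φ(1.96/√φ)], which does not depend on the number of infants.

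| m | μ | CV | φ | SE too small by | Type I error |
|---|---|---|---|---|---|
| 14 | 2 | 0.2 | 1 + 28 × 0.04 = 2.12 | 1.46 | 18 % |
| 30 | 2 | 0.3 | 1 + 60 × 0.09 = 6.40 | 2.53 | 44 % |
| 30 | 3 | 0.4 | 1 + 90 × 0.16 = 15.4 | 3.92 | 62 % |
| 30 | 3 | 0.5 | 1 + 90 × 0.25 = 23.5 | 4.85 | 69 % |

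Simulation with 148 infants per arm agrees, giving 17–68 % over this grid. At m = 30 and μ = 2, simulated type I error was 6.6 % at CV 0.05, 12 % at CV 0.1, 29 % at CV 0.2 and 43 % at CV 0.3. In the same simulations, a Pearson-scaled or infant-level robust standard error brought it back to about 4–6 %.

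**Infant daily averages.** If each infant contributes one mean daily count, its variance/mean ratio is μ·CV² + 1/m.
- Lowest on the grid (m = 30, μ = 2, CV 0.2): 0.08 + 0.033 = 0.11.
- Highest (m = 14, μ = 3, CV 0.5): 0.75 + 0.071 = 0.82.

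The ratio is always below 1, so the Poisson standard error is too large, by 1/√0.82 = 1.10 up to 1/√0.113 = 2.97. Simulated type I error is 0–3 %.

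**Very regular daily counts.** If an infant's counts vary less than Poisson (variance/mean 0.3–0.5), then at m = 30 and μ = 2 the test on totals is conservative when CV is 0.05 (0.5–1.4 %). At CV 0.3 the type I error is again 41 %.

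**The other two Poisson uses.**
- Intolerance episodes, at an assumed variance/mean of 1.75–4.2: type I error 2·[1 − Φ(1.96/√1.75)] = 14 % to 2·[1 − Φ(1.96/√4.2)] = 34 %.
- Yes/no comorbidities: the Poisson standard error is too wide by 1/√(1 − p), which is 1/√0.95 = 1.03 at p = 0.05 and 1/√0.80 = 1.12 at p = 0.20.

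**The case against.** The strongest reply is that a journal article gives each outcome about a sentence, and that unit of analysis, offset and dispersion handling commonly sit in an analysis plan that is not shown. A Poisson model does not exclude a scaled or clustered fit. This stands in part: a reader might infer that the authors have decided to ignore variation between infants, and the article does not say so. But it does commit to a model for this outcome, and in the same paragraph it names a repeated-measures method for growth and none for stools. Nothing in it points to a scaled or clustered fit.

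The second reply is that even the direction of error depends on an unstated unit. This is correct. The endpoint's wording can be read as an infant's daily average, and an unscaled Poisson test would then be conservative. A reader might conclude that false positive findings are certain; the documents do not support that. Nor does the reply rescue the plan, because the model-based standard error is generally wrong under either reading.

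Third, all inputs to the size are assumed, and the calculation has no covariates. This also stands. Adjustment lowers the residual CV, but at a mean of 2 over 30 days a residual CV of 0.1 still gives 12 %.

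Finally, a reader might extend the point to the trial's main result or to every Poisson analysis. The intolerance-count model is only something the authors will consider, the primary test is chi-square on infant-level status, and for comorbidities the error is small and conservative.

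**Conclusion.** The point holds for the stool-frequency endpoint. The article names a Poisson model for a count repeated daily on the same infants and gives no means of handling within-infant correlation or between-infant variation. If infant-days or totals are analysed with the model-based standard error, it is likely too small, with type I error roughly 17–68 % under the assumed values above. If daily averages are analysed, it is too large. The range rests wholly on assumed days, means and CVs, and very regular counts with almost no difference between infants would make even the test on totals conservative.

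The optional intolerance-count model shares the weakness if it is used. The comorbidity effect, a standard error 3–12 % too wide at p = 0.05–0.20, is minor.

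**What to change.** State that spontaneous stool counts will be analysed with log(days observed) as offset and the same baseline covariates. Use either a negative binomial model on infant totals or a Poisson GEE on infant-days with robust standard errors clustered by infant. Name the unit of analysis, and say how stools after an enema are treated, since enemas are recorded daily.

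If the intolerance-count model is used, give it the same robust or negative binomial variance and a days offset. For comorbidities, a robust variance would remove the slight excess width; this is optional.

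The change needs only wording and standard SAS procedures, with no new data. The drawback is a less favourable p value for stool frequency if the counts are overdispersed.

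### Daily stool counts are to be compared with a Poisson model that names no term for within-infant correlation or overdispersion, so the standard errors will be wrong if it is fitted as written

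*Protocol article*

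**What the plan says.** The Outcomes section of the protocol article lists "daily spontaneous fecal discharge conditions" as the fifth secondary endpoint, and the secondary objective includes a benefit on spontaneous stooling. The section on data collected during the NICU stay shows that the raw data are daily records for each infant: "The number of daily bowel movements, times of daily enema, trait and color of stool every time".

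Under Statistical analysis, Secondary outcome, the comparison is given in one sentence: "The number of times of self-defecating per day will be compared using the Poisson model adjusting for baseline covariates". No unit of analysis, offset, infant effect, robust variance or dispersion parameter is named. The same paragraph says that growth, also measured repeatedly in each infant, "will be analyzed using repeated measurement analysis of covariance models".

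**The concern.** Each infant supplies one count per day for the whole stay. Some infants habitually pass more stools than others, so counts from the same infant are alike. Variation is to be expected here, because the Stage I section makes feeding start, route and volume depend on gestational age, birth weight and illness. Baseline covariates remove only the part of that variation which they explain.

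A Poisson regression fixes the variance at the mean. It has no room for extra variation between infants and, on daily rows, no recognition that the rows come in clusters. At stake is the validity of the p value and interval for a listed secondary endpoint tied to a stated objective: a significant effect on stooling could appear with no effect of the formula.

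**Working it through.** **The plan's own figure.** There is none to reproduce. The article gives no stool rate, variance, correlation or error rate for this endpoint.

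**Inputs.**
- Significance level 0.05. The article states this for the primary outcome; I assume it applies here and is two-sided.
- Recorded days per infant, T: not given. The discharge criteria require a corrected gestational age of at least 34 weeks, and infants are admitted immediately after birth. Birth at 32, 30 or 28 weeks therefore implies at least 14, 28 or 42 days. I assume T = 25 and also show 14 and 42.
- Mean stools per day, μ: not given; assumed 2.
- Between-infant CV of the stool rate, after covariate adjustment: not given; assumed 0.1 to 0.5.

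**Case 1: rows are infant-days, or infant totals with a log(days) offset.** These two fits are equivalent: on one simulated data set both gave a coefficient of 0.0263 with standard error 0.0150. Collapsing to totals is therefore no cure by itself. If infant rates vary with the given CV and daily counts are Poisson around each infant's own rate, the true variance exceeds the Poisson variance by

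D = 1 + T × μ × CV²,

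and the actual two-sided type I error is 2 × [1 − Φ(1.96/√D)].

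With T × μ = 25 × 2 = 50:

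| CV | D | 1.96/√D | Type I error |
|---|---|---|---|
| 0.1 | 1 + 50 × 0.01 = 1.5 | 1.60 | 11 % |
| 0.2 | 1 + 50 × 0.04 = 3.0 | 1.13 | 26 % |
| 0.3 | 1 + 50 × 0.09 = 5.5 | 0.84 | 40 % |
| 0.5 | 1 + 50 × 0.25 = 13.5 | 0.53 | 59 % |

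The number of infants does not enter, so a larger trial would not help.

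**Sensitivity.**
- Going from 14 to 42 days at μ = 2, the error is 18 % to 35 % at CV 0.2 and 30 % to 50 % at CV 0.3.
- Over T = 14–45, μ = 1–3 and CV = 0.1–0.6 it runs from about 7 % to 78 %.
- If daily counts within an infant vary half as much as Poisson, replace the leading 1 in D by 0.5. At T = 25 and μ = 2 this gives D = 1.0, 2.5, 5.0 and 13.0, and errors of 5 %, 21 %, 38 % and 59 %. At CV 0.1 the inflation disappears; with short stays and low rates the test becomes conservative (1.4 % at T = 14, μ = 1).

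**Simulation check.** With 148 infants per arm (the completers in the sample size section), stays of 15–45 days, 2 stools a day, gamma-distributed infant rates and 4,000 runs:

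| CV | Plain Poisson | Infant-level robust variance |
|---|---|---|
| 0 | 5.4 % | 5.5 % |
| 0.2 | 31 % | 5.1 % |
| 0.3 | 45 % | 5.0 % |
| 0.5 | 64 % | 5.1 % |

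The plain-Poisson figures exceed the 25-day table because the mean stay is 30 days and stays are unequal. Pearson scaling of the infant totals gave 5.7–6.0 % at CV 0.2–0.5.

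**Case 2: one average per infant, entered as a Poisson outcome.** The true variance of an infant's average is μ/T + μ² × CV² = 2/25 + 4 × 0.09 = 0.08 + 0.36 = 0.44 at CV 0.3. The Poisson model assumes μ = 2. Standard errors are too large by √(2/0.44) = 2.1, so a real difference would tend to be missed.

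**The case against.** The strongest reply is that the article names only a Poisson model. It does not say that the fit is plain, that the unit is the infant-day, or that days are taken as independent. A Poisson GEE with robust variance or a random-intercept Poisson model, adjusted for baseline covariates, would still match the sentence. Variance estimators and offsets are often left to an analysis plan, which is not shown here. The use of a repeated-measures model for growth shows that the authors know such methods.

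Much of this stands. A reader might infer that the plan treats infant-days as independent and that false positives for this endpoint will run at 30–60 %. The text supports neither. The unit is not stated, the direction of error depends on it (too liberal on daily rows or totals, too conservative on averages), and any percentage rests on an assumed stool rate, stay and CV. The relevant CV is also the residual one, and covariates may absorb part of it.

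The point survives in conditional form. The growth sentence shows that the article does state its handling of repeated data where it was planned. The natural reading of the stool sentence is an ordinary Poisson regression, and none of the three ways of feeding these data to one gives right standard errors in general. That is a poorly fitting named model rather than only an omitted detail.

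**Conclusion.** The concern holds conditionally. If the Poisson model is fitted as named, error bars for the stool-frequency endpoint are wrong: too small on infant-days or totals when infants differ beyond the covariates, and too large on per-infant averages. Under the illustrative 25 days and 2 stools a day, the type I error for the first two layouts is about 11 % to 59 % for a residual CV of 0.1 to 0.5. These are illustrations under assumptions, not properties of the plan, and at low CV with underdispersed daily counts the excess can vanish. The firm part is that the article names a model for clustered counts without the term that would make its inference valid. It concerns one secondary endpoint; the chi-square test of the primary outcome is untouched.

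**What to change.** In the Secondary outcome paragraph of the analysis section, name one of the following for daily stool counts, keeping the planned baseline covariates:
- a Poisson or negative-binomial GEE with infant as the cluster and robust variance;
- a count model with a random infant intercept;
- one row per infant (total stools, log of recorded days as offset) with robust or negative-binomial variance.

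State the unit of analysis in the same sentence. The cost is one sentence and a REPEATED or RANDOM statement in SAS, with no new data. Where infants differ, intervals for this endpoint will be wider than a plain Poisson fit to daily rows or totals would show.
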